### Participant recruitment and randomization

Patients will be recruited in clinic at the typical 90-min appointment scheduled with a registered nurse at approximately 8 weeks of pregnancy. The targeted patient population for this study will be low-risk patients. The study coordinator will ascertain the patient’s interest in participating in the study and study eligibility, and a written consent form will be shared with eligible patients. Inclusion criteria include age 18 to 36 years at time of enrollment (older patients excluded under the definition of advanced maternal age as a criterion for risk), documented gestational age less than 13 weeks, pregnancy documented as low risk without a concurrent medical or obstetric complication, ability to read and understand English, and ability to provide informed consent. Women will be excluded if they have any of the conditions listed in the patient enrollment exclusion criteria [see Additional file 1]. Randomization will be conducted using a dynamic allocation [26] algorithm minimizing imbalances across multiple assigned stratification factors. Patients will be stratified by enrolling age (≥35 vs. <35), BMI (>30 vs. ≤30) and parity (0 vs. 1+). A physician will confirm OB Nest patients’ risk assessment at the new OB return appointment at approximately 12 weeks gestation, consistent with current practice workflow. Patients determined to be high-risk at that time will be removed from the study (post-randomization exclusion). We expect exclusions to be minimal due to the clarity of inclusion/exclusion criteria and the availability of physicians as needed for patient eligibility questions during the initial 8-week visit.

Patients randomized to the OB Nest program will be assigned to a dedicated nursing care team comprised of three registered nurses, and they will be scheduled for 8 pre-planned office visits with a provider (physician or CNM) compared to 12 in the usual care group, as shown in Table 3. The 4 office visits will be replaced with connected care visits (phone or online patient portal) with one of the nurses, whom patients can also contact with on-demand questions. There will also be two additional connected care visits in the OB Nest schedule, making total contacts greater in the OB Nest group, even though office visits are reduced. An electronic population management registry was developed on the Caradigm platform for care team management of OB Nest patients. Patients will be listed for the week that the nurse team is to contact them, and lab and imaging tests that have been completed will populate the registry in real time from the electronic medical record. The registry will also send data (task lists) to the clinical team daily based on the protocol of care designed for this initiative.

**Table 3 Tab3:** Comparison of visit schedule by week of gestation, usual care and OB Nest groups

Week	Usual care group	OB nest group	Care provided (both groups)
1-7	Drop-in pregnancy education	Drop-in pregnancy education	Interactive self-education
8	New OB office visit with registered nurse/CNM	New OB office visit with registered nurse/CNM	Individualized pregnancy education, bedside ultrasound, history, lab ordering, discuss genetic options
12	New OB office visit with physician/CNM	New OB office visit with physician	Physical exam including pap if needed and review plan of care
16		Connected care visit with registered nurse^a^	Education and review of care
18	Ultrasound, registered nurse visit	Ultrasound, registered nurse visit	Ultrasound; mid-pregnancy education
24	Routine OB office visit with physician/CNM	Connected care visit with registered nurse^a^	Routine^b^
28	Routine OB office visit with physician/CNM	Routine OB office visit with physician/CNM	Routine^b^ (lab ordering)
33	Routine OB office visit with physician/CNM	Connected care visit with registered nurse^a^	Routine^b^
36	Routine OB office visit with physician/CNM	Routine OB office visit with physician/CNM	Routine^b^ (lab ordering)
38	Routine OB office visit with physician/CNM	Connected care visit with registered nurse^a^	Routine^b^
39	Routine OB office visit with physician/CNM	Routine OB office visit with physician/CNM	Routine^b^
40	Routine OB office visit with physician/CNM	Connected care visit with registered nurse^a^	Routine^b^
41	Routine OB office visit with physician/CNM; registered nurse visit; ultrasound	Routine OB office visit with physician/CNM; nurse visit; ultrasound	Over 40 weeks bi-weekly monitoring
1 week Postpartum		Connected care visit with registered nurse^a^	Education and review of care
8 weeks Postpartum	Routine OB visit with physician/CNM	Routine OB Office visit with physician/CNM	
Total visits to clinic	12	8	

Abbr: CNM = Certified Nurse Midwife

^a^Connected care visits with nurses are scheduled contacts by phone or online patient portal

^b^Routine = Check maternal blood pressure, maternal weight, and fetal heart rate, and provide education

Compared to usual care, OB Nest patients will have 4 fewer office visits. However, total scheduled contacts during pregnancy are greater in the OB Nest group. In addition to changing provider office visits with nurse virtual connected care visits, there are additional nurse contacts at 16 weeks and one week postpartum

Patients will be able to request additional in-office visits if desired and providers may suggest additional in-office visits to monitor maternal or fetal concerns. Laboratory tests, imaging, and standardized evaluations will be conducted in both arms of the study. OB Nest patients will be invited to participate in an online, nurse-moderated community with other OB Nest participants, where they can seek advice and support from their peers. Finally, OB Nest patients will be provided a fetal Doppler and automated blood pressure machine for home use, along with training on how to use the equipment. This equipment will allow patients to monitor their health and provide an opportunity for others to be involved in these experiences outside of office visits. Patients will be asked to keep a weekly journal of weight, fetal heart rate, and blood pressure readings and report those to nurses at the connected care visits.

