### Analysis plan

#### Quantitative (QUAN)

Quantitative analysis will be performed according to the intention to treat principle, including all participants in the arm to which they were randomized, regardless of whether they received the intervention assigned or crossed over to the other treatment arm. Baseline characteristics will be reported in the study results with continuous values being reported as means and standard deviations and categorical values reported as counts and frequencies and compared between study arms using t-tests and chi-squared tests, respectively.

We will use standard techniques appropriate for participant level randomized trials, with each outcome compared between study arms using t-tests for continuous outcomes and chi-square tests for dichotomous outcomes. Any baseline imbalances (*p* < 0.05) will be explored as a possible factor to adjust for when the outcome measures are analyzed. We will use predetermined criteria for missing data when calculating scores on patient-reported surveys. The comparison of outcomes will be considered significantly different between arms at a *P* < 0.05.

Participants who move into a high risk category after 12 weeks will stay on study and be evaluated in the arm to which they were randomized. If more than 10 % of patients choose to crossover from intervention to control, a sensitivity analysis will be conducted. Trial enrollment, completeness of data collection, and fidelity of follow-up procedures will be reviewed and reported during study team meetings which will be conducted on a monthly basis. Analysis of quantitative data will be performed at the close of the study.

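### Women found high-risk at about 12 weeks are removed after randomisation, contradicting the intention-to-treat statement; the check is described only for OB Nest, so comparability is not guaranteed

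*Protocol article*

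**What the plan says.** All places are in the protocol article.

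- **Participant recruitment and randomization.** Women are recruited at a visit at about 8 weeks and randomised by dynamic allocation. Then: "A physician will confirm OB Nest patients’ risk assessment at the new OB return appointment at approximately 12 weeks gestation". The next sentence reads: "Patients determined to be high-risk at that time will be removed from the study (post-randomization exclusion"). On numbers, the section says only: "We expect exclusions to be minimal due to the clarity of inclusion/exclusion criteria".
- **Table 3, week 12.** The usual-care entry is "New OB office visit with physician/CNM". The OB Nest entry names a physician only.
- **Sample size.** 150 women per arm are enrolled. Withdrawal and post-randomisation exclusion together may reach 10%, leaving 135 per arm.
- **Analysis plan, Quantitative (QUAN).** The analysis follows intention to treat, "including all participants in the arm to which they were randomized, regardless of whether they received the intervention assigned". A separate rule covers later reclassification: "Participants who move into a high risk category after 12 weeks will stay on study and be evaluated in the arm to which they were" randomised.

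**The concern.** There are two linked problems.

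The first is a contradiction. One section takes a group of randomised women out of the study, and another says that all randomised participants are analysed. The Sample size section deducts exclusions from the effective number, so removal appears to mean loss from the analysis and not merely a change of care. The analysis plan retains women who become high-risk after 12 weeks and does not say how those removed at 12 weeks fit its intention-to-treat statement. The conflict exists even if both arms are handled identically.

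The second is possible selection by arm. The check is worded for OB Nest patients, and no matching check is described for usual care. High-risk status is prognostic for visits, hospitalisation, birth weight and gestational age. If more high-risk women leave OB Nest than leave usual care, OB Nest would look better on utilisation and on maternal/fetal safety without any true effect. Those outcomes make up the second research question. Record abstraction starts at enrolment, so a complication arising before the 12-week visit could be both a recorded outcome and a reason for removal. That last step is an inference from the text.

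**Working it through.** **1. The plan's own figures.** 150 × (1 − 0.10) = 135 per arm, as stated. For satisfaction, the difference is 115.6 − 108.4 = 7.2 with SD 14.4 (0.5 SD), two-sided alpha 0.05. Power at 135 per arm is 98.4%, against 98% in Table 2. It is 99.1% at 150 per arm and 98.8% at 135 versus 150. Power is therefore not the issue; bias is.

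**2. Bias formula.** Let a fraction f be removed from OB Nest only, and let the removed women's mean differ from that of the remaining women by D. With no true effect, the spurious difference between arms is f × D. The type I error by normal approximation is Φ(−1.96 + b/se) + Φ(−1.96 − b/se). Here b = f × D in SD units and se = √(1/(150(1−f)) + 1/150).

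**3. Inputs not in the document.** Neither f nor D is given. f = 2% (3 of 150 women) stands for few exclusions. f = 10% (15 women) is an upper bound that uses the whole combined allowance. The gaps of 5 visits and 30% low birth weight are assumptions.

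**4. Antenatal visits** (Table 2: SD 4.2; planned difference 14.7 − 12 = 2.7).
- f = 2%: 0.02 × 5 = 0.1 visit, and 0.1/2.7 = 4% of the planned difference. b = 0.1/4.2 = 0.024, se = √(1/147 + 1/150) = 0.116, b/se = 0.205. Type I error is about 5.5%.
- f = 10%: 0.10 × 5 = 0.5 visit, and 0.5/2.7 = 19%. b = 0.5/4.2 = 0.119, se = √(1/135 + 1/150) = 0.119, b/se = 1.00. Type I error is about 17%.
- The 5-visit gap is 5/4.2 = 1.19 SD, which is large. With gaps of 0.25 to 1.0 SD, type I error is 5.0–5.3% at f = 2% and 5.5–13.5% at f = 10%.

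**5. Low birth weight** (Table 2: 11% in usual care, 6% targeted). The OB Nest rate after removal is (0.11 − f × 0.30)/(1 − f).
- f = 2%: 0.104/0.98 = 10.6%, a spurious gain of 0.4 percentage points.
- f = 10%: 0.080/0.90 = 8.9%, a spurious gain of 2.1 points.
- If removed women instead have 2 to 3 times the risk of the others, the gain is 0.2–0.4 points at f = 2% and 1.0–1.8 points at f = 10%.

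**6. Satisfaction (primary outcome).** With D = 0.25 to 1.0 SD, the shift is 0.07–0.29 points at f = 2% (1–4% of 7.2) and 0.36–1.44 points at f = 10% (5–20% of 7.2). These are absolute sizes. The document gives no basis for the sign.

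**The case against.** The strongest reply is that one-sided removal is inferred, not stated. Only the confirming sentence names OB Nest patients; the removal sentence speaks of patients without qualification. The article describes the "risk assessment at the new OB return appointment at approximately 12 weeks gestation, consistent with current practice workflow", which suggests a routine assessment and not a gate created for one arm. Table 3 gives both arms a week-12 visit with the same listed care, and the Sample size section applies its allowance to both arms. This stands. A reader might infer that high-risk women certainly leave OB Nest and stay in usual care, so that the arms are no longer comparable. The documents do not support that certainty.

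A reader might also infer that the checking physician knows the allocation. The article does not say so. Because the check is worded by arm, however, masking cannot be assumed.

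The 10% scenarios deserve limited weight. That allowance covers withdrawals as well as exclusions, in both arms, and the article expects few exclusions because the criteria are clear and physicians are available at the 8-week visit. Low birth weight has only 24% planned power, and the article acknowledges that it is underpowered.

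None of this removes the contradiction with intention to treat. The expectation of few exclusions carries no number or cap. Even if both arms are assessed, Table 3 names different assessors.

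**Conclusion.** The point holds as an unreconciled contradiction between the 12-week removal and the intention-to-treat statement, together with a check that is described for one arm only. As the text stands, comparability after 12 weeks is no longer guaranteed by randomisation. Whether it is actually lost depends on how usual-care women are handled, which the article does not make clear.

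If handling differs by arm, utilisation and maternal/fetal outcomes could be biased in favour of OB Nest. With few exclusions (2%), the distortion is small on every outcome examined, even under the assumed gaps of 5 visits and 30% low birth weight. It becomes material only towards the 10% upper bound, which would require the whole allowance to fall on OB Nest exclusions. The true size is unknown, because the document gives neither the share removed nor the prognosis of those women.

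**What to change.** - Delete the 12-week removal from the analysis rules. Keep all randomised women in both arms in follow-up and in the primary analysis in their randomised arm. This extends the rule that the Analysis plan already applies to women reclassified after 12 weeks. Clinical care stays with the clinicians.
- State any 12-week risk assessment that is kept identically for both arms, and say that it does not determine inclusion in the analysis.
- For women already removed (the article says enrolment is under way), abstract records where consent and ethics approval allow. Record abstraction cannot recover a missed 36-week survey, so treat missed surveys as missing data.

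The cost is a change of wording, surveys and abstraction for the few women who would otherwise be lost, and slight dilution from women whose care changes. The planned 300 women are unchanged, and power for satisfaction stays at 98–99%.

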### Data collection

#### Quantitative (QUAN)

Patient characteristics will be collected for patients in both arms (*n* = 300) at time of enrollment through self-report and medical record review including: age, race/ethnicity, education level, marital status, body mass index (BMI), due date, parity, previous miscarriage, previous C-section, and insurance. The following patient-reported outcome instruments, administered by email or by mail if requested, will be used to provide data on locus of control (collected as a measure of participant characteristics at baseline), satisfaction with care, quality of care, and stress related to pregnancy in both arms:The validated Fetal Health Locus of Control Scale will be used at the time of enrollment to assess patients’ feelings of control in their pregnancies [27]. The scale contains 18 items, with 6 questions per subscale that address internal control, control by health professionals and control by God/fate/chance. Points will be summed and reported on each subscale.Patient satisfaction (primary outcome) with care will be assessed using the validated 16-item Satisfaction subscale, which is scored on a 5-point scale from ‘very dissatisfied’ to ‘very satisfied.’ The scale will be collected at the 36-week assessment [28]. Responses will be summed and converted to a 0–100 point scale where higher scores are indicative of a higher degree of satisfaction.Patient perceptions of quality of care will be assessed using the validated Prenatal Interpersonal Processes of Care (PIPC) scale [29]. The 30 items cover 3 subscales that address communication, decision making and interpersonal style. The scale will be collected at the 36 week assessment. Responses will be converted to a 0–100 scale for each subscale.Stress will be evaluated using the validated PreNatal Maternal Stress (PNMS) scale [30]. The 9-item scale will be emailed to patients at approximately 14 weeks gestation and again with additional items at approximately 24 weeks and 26 weeks gestation. Scores will be summed and averaged where higher scores are indicative of a higher degree of stress.

Data from the medical record will be abstracted to capture utilization, fidelity to standards of prenatal care, and maternal/fetal outcomes. The time frame for collection will be from time of enrollment to the 6–8 week postpartum appointment. Medical record review will be conducted to capture all in-office obstetrics visits, assessments in the out-patient OB triage center, and hospitalizations. It will also be used to track clinically-important outcomes including incidence and dates of pre-eclampsia/eclampsia, hypertension, anemia, urinary tract infection, hematocrit, infection, and loss of pregnancy. Assessment at the time of delivery will include maternal weight gain, type of delivery, length of stay during hospitalization, gestational age at delivery, birth weight, and Apgar scores. To assess compliance with standard processes of care, study staff will review the medical record for patients in both arms against a list of ACOG standards of prenatal care, for example depression screening, HIV testing, prenatal vitamin/iron supplement prescription, offering influenza vaccine, and screening for gestational diabetes.

Utilization data from the medical record will be supplemented by data from an internal data tracking system used to detail OB Nest patient and nursing contact, including numbers of phone calls, on-line visits, and conversations through the secure online patient portal. Nurses will also track time spent on OB Nest patient care in a department time tracking system. These data, along with average assessments of time spent on in-office visits (provider, rooming nurse and desk staff) and FTE calculations provided by department financial staff, will be used to assess staffing demands in both arms.

#### Qualitative (qual)

Qualitative one-on-one interviews and asynchronous online focus groups (online discussion boards where individuals are not required to participate in real-time) will be used to gather data on perceptions of quality and satisfaction. OB Nest participants will be sampled from a list of those who indicated interest during the consent process. We hypothesize that a woman’s experience will differ by whether she is a first time mother or not, so we will stratify based on parity.

We will complete individual semi-structured interviews with up to 40 OB Nest patients. Interviews, conducted by a trained qualitative interviewer, will be approximately 30-min in length and typically conducted by phone. Because we want to interview patients after significant exposure to intervention activities, we will aim to conduct the interview when the patient reaches 28 and 32 weeks gestation. Patient focus group data collection (4 groups of 10–12 patients each) will begin after interview data collection. The asynchronous online focus groups will be open for a week, with new topics and questions posted each day by the moderator (a member of the research team). The topics and questions will be semi-structured and based on the initial analysis of the individual patient interviews. The online asynchronous nature of the groups means participants will be able to sign on at a time and place that is convenient for them.

Interviews and discussions with providers, nurses, and desk staff/clinical assistants will be used to gather information on staff perceptions of the intervention and its implementation. We will invite all physicians, nurse midwives, nurses, desk staff, and clinical assistants involved in the study to provide qualitative data. Data collection will happen at three time points during the study: baseline (first month of the study), mid-point, and end of study. Interview guides will be semi-structured and will include questions based on the RE-AIM framework, as well as Normalization Process Theory, which is a sociological theory of the implementation, embedding, and integration of new technologies and organizational innovations in complex settings [31, 32]. This theory informed questions on how providers and staff understand the purpose of OB Nest and its value in their practice, how they perceive the impact it will have on their work, whether appraisal has led to changes in practice, and whether people are engaged in driving the initiative forward, for example.

Finally, document review, which will involve capturing the written documents from OB Nest implementation (eg, presentations and memos about OB Nest), will further help us understand how it was perceived and what contextual factors may have shaped implementation.

### Analysis plan

#### Quantitative (QUAN)

Quantitative analysis will be performed according to the intention to treat principle, including all participants in the arm to which they were randomized, regardless of whether they received the intervention assigned or crossed over to the other treatment arm. Baseline characteristics will be reported in the study results with continuous values being reported as means and standard deviations and categorical values reported as counts and frequencies and compared between study arms using t-tests and chi-squared tests, respectively.

We will use standard techniques appropriate for participant level randomized trials, with each outcome compared between study arms using t-tests for continuous outcomes and chi-square tests for dichotomous outcomes. Any baseline imbalances (*p* < 0.05) will be explored as a possible factor to adjust for when the outcome measures are analyzed. We will use predetermined criteria for missing data when calculating scores on patient-reported surveys. The comparison of outcomes will be considered significantly different between arms at a *P* < 0.05.

Participants who move into a high risk category after 12 weeks will stay on study and be evaluated in the arm to which they were randomized. If more than 10 % of patients choose to crossover from intervention to control, a sensitivity analysis will be conducted. Trial enrollment, completeness of data collection, and fidelity of follow-up procedures will be reviewed and reported during study team meetings which will be conducted on a monthly basis. Analysis of quantitative data will be performed at the close of the study.

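### Allocation is minimised on age, BMI and parity, but outcomes are compared by unadjusted tests, and the only route to adjustment is a baseline p<0.05 trigger that almost never flags those factors

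*Protocol article*

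**What the plan says.** Protocol article, Participant recruitment and randomization: "Randomization will be conducted using a dynamic allocation [26] algorithm minimizing imbalances across multiple assigned stratification factors". The factors are age at enrolment (35 and over against under 35), BMI (above 30 against 30 or below) and parity (0 against 1 or more).

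Protocol article, Analysis plan, Quantitative (QUAN), fixes three things:

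- Outcomes: "each outcome compared between study arms using t-tests for continuous outcomes and chi-square tests for dichotomous outcomes". No allocation factor is named.
- Baseline characteristics are "compared between study arms using t-tests and chi-squared tests, respectively".
- A baseline variable with p<0.05 in that comparison "will be explored as a possible factor to adjust for when the outcome measures are analyzed". No model is named, and nothing says whether the adjusted or the unadjusted result is primary.

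The baseline variables, in Data collection, Quantitative (QUAN), are "age, race/ethnicity, education level, marital status, body mass index (BMI), due date, parity, previous miscarriage, previous C-section, and insurance", plus three subscales of the Fetal Health Locus of Control Scale.

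**The concern.** Minimisation forces the arms to agree on three factors. If those factors predict the outcome, their contribution to the between-arm difference is largely removed by design. A t-test still counts it in the standard error. The standard error is then too large, the interval too wide and the test conservative.

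The stated route to adjustment does not repair this. A significance test for imbalance is least likely to flag the variables that were balanced on purpose. For the remaining variables, randomisation makes every null hypothesis of no baseline difference true, so a p-value below 0.05 reflects chance and says nothing about prognostic value. Because a flagged variable is only explored, the choice between adjusted and unadjusted results is left until after the data are seen.

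**Working it through.** **Inputs from the protocol article.** 150 per arm, as few as 135 after 10% loss; two-sided alpha 0.05 (Sample size). Satisfaction 108.4 against 115.6, SD 14.4, power 98%; quality of care 83.9 against 91.9, SD 22.8, power 86% (Table 2). Ten baseline characteristics, three of which underlie minimisation factors, so seven do not; three locus-of-control subscales bring the non-minimised total to 10.

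**Assumption.** R², the share of outcome variance explained by the three factors, is not given. A range from 2% to 20% is shown.

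**1. The plan's own figure.** Power = Φ(d·√(n/2) − 1.96). For satisfaction d = 7.2/14.4 = 0.5, so at 135 per arm 0.5 × √67.5 = 4.108 and Φ(2.148) = 98.4%. The stated 98% reproduces.

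**2. Type I error of the unadjusted test.** With perfect balance on the factors, the true variance of the difference is (1 − R²) times what the t-test assumes, so alpha = 2·(1 − Φ(1.96/√(1 − R²))).

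| R² (assumed) | 1.96/√(1 − R²) | Type I error |
|---|---|---|
| 2% | 1.980 | 4.8% |
| 5% | 2.011 | 4.4% |
| 10% | 2.066 | 3.9% |
| 20% | 2.191 | 2.8% |

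A simulation of minimisation agrees in direction. It used 3,000 trials per setting, 300 patients with 10% random loss and a biased coin of 0.7, 0.8 or 1.0. The distributions were assumed: age mean 29 and SD 4, truncated to the entry range; BMI median 26; a 55:45 parity split. Unadjusted type I error was 4.5–4.9% at R² 5%, 4.0–4.5% at 10% and 3.1–3.6% at 20%. The model adjusted for the three factors gave 5.1–5.4%.

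**3. What the trigger flags among the minimised factors.** In the same simulation the dichotomised factors reached p<0.05 in 0 to 0.07% of trials, against about 5% under simple 1:1 randomisation. Tested as continuous variables, age was flagged in about 2.6–2.9% of trials and BMI in about 0.2–0.3%.

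**4. What it flags elsewhere.** For k independent tests, P(at least one p<0.05) = 1 − 0.95^k. For k = 7 this is 30%; for k = 10 it is 40%.

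**5. Power at 135 per arm.** Adjusted power = Φ(d·√(n/2)/√(1 − R²) − 1.96).

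- Satisfaction, R² 10%: Φ(4.108/0.949 − 1.96) = Φ(2.370) = 99.1%, against 98.4% from the unadjusted formula.
- Quality of care: d = 8.0/22.8 = 0.351 and 0.351 × √67.5 = 2.883. Unadjusted formula: Φ(0.923) = 82.2%. Adjusted: 84.1% at R² 5% and 86.0% at 10%. (Table 2's 86% is the unadjusted figure at 150 per arm.) Under perfect balance the t-test does slightly better than its formula, Φ(0.923/√0.9) = 83.5% at R² 10%, so the gain from adjustment within this design is nearer 2.5 points than 4.
- A smaller true effect, d = 0.3, simulated: about 70% unadjusted; adjusted about 74% at R² 10% and 78–79% at 20%.

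**The case against.** The case on the other side is mostly about size, and much of it stands.

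- **The factors may predict little.** Entry stops at age 36, so the ≥35 stratum covers only ages 35 and 36 and may be sparse. At R² of 2–5% the loss is hard to tell from none.
- **The error is in the safe direction.** The unadjusted test does not inflate false positives.
- **The primary outcome is barely touched.** A reader might infer that power is materially lost on every outcome. At the planned difference, satisfaction has at least 98% power either way.
- **The trigger can select a minimised factor.** A reader might infer that it never can. The plan compares continuous baseline values by t-test, so age, and rarely BMI, could be flagged in that form.
- **The trigger does not define the final model.** A flagged variable is only explored. The fair criticism is that the deciding result is left open. A large type I error cost from the trigger has not been shown.
- **The 30% and 40% assume independence.** Previous C-section is possible only in parous women, and the three subscales come from one questionnaire.
- **Parity.** A reader might cite the expectation that a woman's "experience will differ by whether she is a first time mother or not" as the protocol's own statement that parity predicts the outcome. That sentence justifies stratified sampling for interviews and focus groups; it says nothing about the 36-week satisfaction score.
- **Logistic models can strain.** Low birth weight at 11% and 6% gives about 135 × 0.11 + 135 × 0.06 ≈ 23 events.

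None of this removes the mismatch. It is not a detail left to an unseen analysis plan either, because the article itself fixes both the unadjusted tests and the trigger.

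**Conclusion.** The point holds in a limited form. The analysis leaves out the factors used to allocate patients, and its one adjustment rule almost never reaches them as dichotomised while flagging other variables by chance. The result is a conservative test and an unspecified choice between adjusted and unadjusted results. The conservatism rests on an assumed R² and near-perfect balance, and it approaches zero if the factors are weakly prognostic. The planned primary comparison is not at risk; the practical loss falls on quality of care and on true effects smaller than planned. It should be changed because the remedy costs almost nothing.

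**What to change.** - **Continuous outcomes:** pre-specify as primary a linear model with arm plus age, BMI and parity in the categories used for allocation.
- **Dichotomous outcomes:** logistic regression with the same factors, reported as a standardised risk difference. State a fallback for few events, as for low birth weight: for example, drop the sparse ≥35 factor or use the unadjusted test.
- **Delete** the between-arm baseline significance tests and the p<0.05 trigger. Report baseline characteristics descriptively.
- **Keep** the t-tests and chi-square tests as supporting analyses, and say that the adjusted result decides.

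The cost is a few lines of wording. All three factors are already collected at enrolment, and no extra patients are needed.
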